## Abstract

Various factors, such as fear of falling, postural instability, and altered executive function, contribute to the high risk of falling in Parkinson's disease (PD). Dual-task training is an established method to reduce this risk. Motor-perceptual task combinations typically require a patient to walk while simultaneously engaging in a perceptual task. Motor-executive dual-tasking (DT) combines locomotion with executive function tasks. One augmented reality treadmill training (AR-TT) study revealed promising results of a perceptual dual-task training with a markedly reduced frequency of falls especially in patients with PD. We here propose to compare the effects of two types of concurrent tasks, perceptual and executive, on high-intensity TT). Patients will be trained with TT alone, in combination with an augmented reality *perceptual* DT (AR-TT) or with an *executive* DT (Random Number Generation; RNG-TT). The results are expected to inform research on therapeutic strategies for the training of balance in PD.

## Introduction

Falls occur with a high prevalence of about 60% in patients with Parkinson's disease (PD) with 40% having recurrent falls with an average of 20 falls per year (1). Stooped posture, increased sway, turning deficits, slowed integration of somatosensory information, reduced postural, and anticipatory adjustments are important factors contributing to reduced balance (2). Already in an early stage of PD, diminished gait speed, pain, history of falls or near falls, balance disturbances during dual-tasking (DT), retropulsion, freezing of gait (FoG), and the need for stabilization assistance are associated with falls (3). When controlled for age and sex, only fear of falling, history of near falls, and retropulsion predict prospective falls (3). In later stages, the akinetic-rigid motor type, motor fluctuations (off-phases and dyskinesia), high L-dopa dosage, FoG, and anxiety predict falls (4, 5). At these stages, falls are further predicted by impaired postural stability and by impaired cognitive function. In particular, attention, executive function, and specifically the capability of DT predict future falls (6, 7).

Two hypotheses for DT deficits may explain the reduced performance in patients with PD (8). The capacity hypothesis assumes limited frontal-executive resources (9), while the bottleneck hypothesis assumes that the time factor leads to a reduced availability for two different tasks to be performed simultaneously (10). The two views are not mutually exclusive. On the one hand, diminished executive functions may hamper the capacity for motor execution while slowness, especially during dopamine depletion (off-phase), may simply delay motor execution. Another key factor to be considered is reduced automaticity, which requires a compensatory frontal-executive activation as shown in an interventional neuroimaging study (11). In view of reduced automaticity in postural reactions, physiotherapeutic interventions aim at employing goal-directed reward-based training enhancing both motor and cognitive neuroplasticity (12). DT is a widely used methodology for the quantification of performance decrements induced by well-defined task-load (8). In patients with PD, DT reduces step width and step variability already during the early stages (13) presumably due to a wrong prioritization of the cognitive task, which then leads to a deterioration of gait and posture (14). The nature of the dual-task seems to be critical. When “pure motor” and “motor-cognitive” DT were compared, especially motor DT deficits were found to be a predictor of falls (15).

Since physiotherapeutic interventions often failed to report substantial influences on gait stability (16), goal- and reward-based dual-task treadmill training in augmented reality (AR-TT) has been developed (17). By simulating everyday situations, it reduced the frequency of falls as compared to TT alone in elderly persons and patients with PD by training of dual-task capabilities, such as perceptual cueing (17). Neuroimaging analyses revealed diminished frontal but augmented cerebellar activity presumably contributing to increased gait stability following AR-TT with perceptual cues (11). Thus, both motor-perceptual and motor-executive DT appear to be powerful interventions in the training of gait.

Recent AR-TT solutions provide a range of different tasks suitable for PD patients with gait instability, which have to be chosen from the assessors to provide an optimal training adapted to the individual patient. From our experiences and from previous studies, dual-task interventions on the display that include reward games and cueing interventions on the floor are thought to have the greatest impact on gait in PD (17). Since both executive DT and perceptual DT contribute to improved gait performance, we aim at comparing pure TT with a TT combined with the perceptual challenge of AR-TT on the one hand and paired with a simultaneous executive function task on the other hand.

Several reasons made us select random number generation (RNG) as the executive task to be performed simultaneously with walking (RNG-TT). First, ever since Baddeley (18), this task has widely been used in the dual-task literature [see Dirnberger and Jahanshahi (19) for a review], especially also in patients with PD. In this latter context, Brown et al. (20) found that patients reacted opposite to controls when RNG was added to a motor task (manual tracking). Specifically, patients with PD showed an exacerbated bias compared to single-task conditions. The authors concluded that RNG is a useful tool for investigating executive functions, also in PD.

Second, dual-task experiments in patients with PD have previously helped to uncover factors leading to impairments in both cognition and motor action (20). Third, the impact of RNG on treadmill walking has recently been studied by Rodrigues et al. (21), albeit not in patients with PD, but in a group of participants aged 60–85 years. Forth, RNG is a highly demanding task, yet it is playful (there are no “correct” or “incorrect” responses), relatively independent of education (22), and resistant to multiple testing (23). Finally, one advantage of RNG as a dual-task is that performance quality can be exactly quantified. This means that the bidirectional interference (24) between the two tasks performed simultaneously can be fully described (e.g., RNG can reduce step length or impair other measurable gait parameters, but at the same time walking could enhance sequence redundancy or impair other measures of sequential randomness).

## Materials and Methods

### Study Design

Patients with PD will be assigned randomly to one of three different training programs (AR-TT, or RNG- TT, or TT alone), which will be performed in a parallel-group design for 3 weeks of 30 min daily for 5 days a week in addition to the regular rehabilitation program (Figures 1, 2). Frequency of falls or near falls (within 3 months before V1) will be used (x > 1 or x = 1) for stratified randomization.

**Figure 1 F1:**
[figure not shown]
Flowchart of the study.

**Figure 2 F2:**
[figure not shown]
Experimental protocol design. MMSE, Mini-Mental Status Examination; Mini-BEST, Mini-Balance Evaluation Systems Test; SBG, sensor-based gait analyses; FoG, freezing of gait; WOQ-9, Wearing-Off Questionnaire-9; PDQ8, QoL in PD questionnaire; HADS, Hospital Anxiety and Depression Questionnaire; MDS-UPDRS, MDS-sponsored revision of the Unified Parkinson's Disease Rating Scale; CGIC, Clinical Global Impression of Change; TAP, Test Battery of Attentional Performance.

Assessments will be performed by a blinded investigator before the beginning of the training (V1), after 3 weeks of training (V2), and 3 months after training (V3) during the on-phase. The primary outcome will be the frequency of falls or near-falls during 3 months following training compared to the frequency of falls or near-falls in the 3 months before inclusion (AR-TT vs. TT, and RNG-TT vs. TT). Both interventions will be compared in exploratory analyses (AR-TT and RNG-TT).

Secondary outcomes will be the clinical parameters Movement Disorder Society-sponsored revision of the Unified Parkinson's Disease Rating Scale (MDS-UPDRS III-IV) (25), Hospital Anxiety and Depression Questionnaire (HADS) (26), FoG Questionnaire (27), the Mini-Balance Evaluation Systems Test (Mini-BEST) (28), quality of life in PD questionnaire (PDQ-8) (29), Wearing-Off Questionnaire-9 (WOQ-9) (30), and executive function testing by using tests of the Test Battery of Attentional Performance (TAP) (31) assessed at V1, and compared to V2 and V3 (MDS-UPDRS III-IV, HADS, FoG Questionnaire, Mini-BEST only). Clinical Global Impression of Change (CGIC) will be assessed and V2 and V3 (32).

Sensor-based gait (SBG) assessment will be measured and compared before V1, after V2, and before V3 to have more detailed information on gait changes in the natural environment at home. Given the set of parameters described in Section “Gait and Physical Activity Assessment Using Wearable Sensors,” analyses will be conducted to evaluate the sensitivity to change related to a progression in daily-life motor performance following the rehabilitation program. In addition, gait analysis on behalf of the C-Mill data will be collected before and after the intervention during 3 min of comfortable walking (V1 and V2).

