### Sample Size

According to previous studies, a reduction of 50% in the frequency of falls or near falls can be expected in the two experimental intervention groups vs. a reduction of 25% in the control group. Under the assumption of a difference of 1.5 falls between the respective group and placebo and an SD of 1.16, a sample size of 15 patients in each group is required (alpha = 0.025 two-tailed, power = 80%), i.e., 10% dropouts (G-power) (11).

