### Statistics

Numerical variables will be described with means and SDs, and categorical variables by percentages. The numerical outcomes in this study will be analyzed by a mixed-effect ANOVA model, using treatment and visit as fixed factors, subject as a random factor, and baseline values as covariates. A planned contrast will be used to compare data at month 3 between the groups. Non-normally distributed variables will be log-transformed. Imbalances in the characteristics of the groups at baseline will be included in the ANOVA model as part of a sensitivity analysis. The statistical analysis will be conducted in R 4.1.1 (The R Foundation, Vienna, Austria).

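### The primary fall count has one 3-month window, 10% dropout is expected, and the named ANOVA has no term for time observed, so it cannot properly use a leaver's partial follow-up

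*Protocol article*

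**What the plan says.** All references are to the protocol article.

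- **Outcome.** Study Design (text after the Figure 2 legend): "The primary outcome will be the frequency of falls or near-falls during 3 months following training". The yardstick is the same measure over an equally long period ahead of study entry, and each dual-task arm is set against treadmill training alone. There is thus one window before inclusion and one after training. The text does not say whether frequency means a raw count or a rate per unit of time.
- **Sample size.** The Sample Size section expects that "a reduction of 50% in the frequency of falls or near falls can be expected in the two experimental intervention groups"; for controls it takes half that reduction, 25%. It assumes "a difference of 1.5 falls between the respective group and placebo and an SD of 1.16" and concludes that "a sample size of 15 patients in each group is required", with two-sided alpha 0.025 and "power = 80%), i.e., 10% dropouts".
- **Analysis.** Statistics: "The numerical outcomes in this study will be analyzed by a mixed-effect ANOVA model, using treatment and visit as fixed factors". The model also has a random subject effect and adjusts for baseline. The groups are compared by a planned contrast at month 3, and non-normal variables are log-transformed. No offset, person-time or rate denominator is named.

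**The concern.** A mixed model helps with dropout when a leaver has earlier post-baseline values of the same outcome. Here there are none. V2 falls at the end of training, before the 3-month window opens, and the fall count is complete only at V3. For this outcome the visit factor and the random subject effect therefore carry no information about a patient who leaves in between.

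Under the named model such a patient can be treated in two ways. Either the patient is left out, and falls already observed go unused, or the partial count enters as if it covered 3 months.

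In a falls trial, leaving because of a fall or its consequences is plausible. All patients have had at least one fall or near-fall in the 3 months before baseline. If leaving is related to falls, either treatment can remove events preferentially from frequent fallers. If partial counts enter as full ones, an arm observed for less time looks better for that reason alone. At stake is the estimate of the primary comparison, with about 13 evaluable patients per arm.

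**Working it through.** **1. The plan's own figure.** Inputs from Sample Size: difference 1.5, SD 1.16, two-sided alpha 0.025, power 80%, dropout 10%. In a two-sample t-test with the noncentral t distribution, 13 per arm gives noncentrality 1.5 / (1.16 × √(2/13)) = 3.30 and power 81.1%. Then 13 / 0.9 = 14.4, rounded up to 15. The stated 15 per group is reproduced, so it already pays for the loss of 10% of patients. Ten per cent of 45 is 4.5 patients, or 1.5 per arm.

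**2. Implied means (assumption).** A difference of 1.5 falls from reductions of 50% and 25% implies a baseline of 1.5 / (0.50 − 0.25) = 6. The post-training means are then 6 × 0.75 = 4.5 (control) and 6 × 0.50 = 3.0 (experimental).

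**3. Leavers excluded, leaving unrelated to falls.** The expected difference stays 1.5. Power is 81% with 13 per arm, and 82% by simulation with random 10% loss from 15 per arm. There is no bias and the planned power holds.

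**4. Partial counts entered as full counts, leaving unrelated to falls.** Let d be the dropout proportion in an arm and f the fraction of the window that leavers are observed. The document gives no f, so it is varied.

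Expected difference = 4.5 × [1 − d_control(1 − f)] − 3.0 × [1 − d_exp(1 − f)]

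| Dropout control / experimental | f | Difference |
|---|---|---|
| 10% / 10% | 0.75 | 4.3875 − 2.925 = 1.46 |
| 10% / 10% | 0.5 | 4.275 − 2.85 = 1.425 |
| 10% / 10% | 0 | 4.05 − 2.70 = 1.35 |
| 20% / 0% | 0.5 | 4.05 − 3.00 = 1.05 |
| 0% / 20% | 0.5 | 4.50 − 2.70 = 1.80 |

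With equal dropout the difference shrinks by about 5% at f = 0.5 and by at most 10%. With unequal dropout it can shrink or grow. Power with 15 per arm is 87% with complete follow-up. With 10% dropout in each arm, allowing for the added variance, it is about 77% at f = 0.5 and 49–85% for f from 0 to 0.75. It is 72% by simulation with uniform leaving times.

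**5. Leaving related to falls.** Assumptions, none of them in the document: each event has a 3% chance of causing withdrawal (about 8% and 12% dropout in the two arms), and counts are gamma-Poisson with shape 1, shape 2 or no overdispersion. For completers only, the bias in the arm difference is:

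| Counts | Unadjusted means | Baseline covariate | Baseline covariate and log(y+1) |
|---|---|---|---|
| Shape 1 | −20% | −13% | −5% |
| Shape 2 | −12% | −9% | −4% |
| No overdispersion | −3% | −3% | under −1% |

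Partial counts entered as full give about −8% to −12% on the log scale. A separate check with 15 per arm and a baseline covariate gave 4–14% attenuation for completers and 12–19% for partial counts.

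**6. The alternative model.** The true log rate ratio is ln(3.0 / 4.5) = −0.405. In the same 15-per-arm check, a quasi-Poisson model with log observed time as offset gave about −0.40. Its test size was near or below 0.025, and its power was similar to or slightly better than that of the completer analyses.

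**The case against.** The strongest reply is that the article never says how a patient with less than 3 months of follow-up is handled. It says neither that leavers are excluded nor that partial counts enter uncorrected, and frequency might mean a rate. Such detail commonly sits in a full protocol or analysis plan, which is not shown. That stands: the silence is no fault, and the point here rests only on the model that is named. Reading frequency as a rate would not fully settle it. An ANOVA giving each patient's rate equal weight would treat a few days of follow-up like 3 months.

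A reader might infer that the arm difference necessarily shrinks. The documents do not support this. Random loss of leavers leaves it at 1.5, and unequal dropout with partial counts can enlarge it.

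A reader might also take the unadjusted figures of 12–20% as the size of the problem. They ignore the baseline covariate and log-transformation that the Statistics section names, and they need a withdrawal mechanism that the document does not give; near-falls in particular seem unlikely to make patients leave.

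The overdispersed counts also sit badly with the planned SD of 1.16. With variance mean + mean²/shape, the SDs run from √7.5 = 2.7 to √24.75 = 5.0. At 13 per arm the standard error of the difference is then √(22.125/13) = 1.3 to √(36.75/13) = 1.7, so an unadjusted bias of 0.2–0.3 falls is roughly a fifth of one standard error. This stands, and it limits the size of the point.

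Finally, an offset model naturally does well on data simulated from a constant-rate count process. That is fair, and it is the method's main assumption.

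**Conclusion.** The point holds as a modest weakness in the stated analysis. The 3-month window, the expected 10% dropout and a model without an exposure term are all in the text, and that combination leaves no sound way to use a leaver's observed falls.

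The size depends on what happens:

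- **Random loss, leavers excluded:** no bias, and power is already covered.
- **Partial counts as full counts, equal 10% dropout:** about 5% shrinkage, at most 10%, with lower power.
- **Partial counts as full counts, unequal dropout:** bias in either direction.
- **Leaving caused by falls (assumed 3% per event, overdispersed counts):** roughly 4–19% toward no effect, and little for completers without overdispersion.

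The last range rests on assumptions about withdrawal and overdispersion that the document neither states nor rules out. The documents do not show that partial counts will be entered uncorrected, or that the result will be biased in a known direction. The change is worth making because it is cheap and removes the dependence on which arm was observed for longer.

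**What to change.** - **Study Design:** define the primary outcome as the rate of falls or near-falls over the observed time, up to 3 months after training.
- **Data:** record the date of last fall information for every randomised patient, including those who stop training or miss V3.
- **Statistics:** analyse all randomised patients with any follow-up in an overdispersed count model (negative binomial or quasi-Poisson) with log(days observed) as offset and with treatment and log baseline count as covariates. Use a t-based reference because the arms are small. The log baseline count is always defined, since entry requires at least one event in the 3 months before baseline.

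The cost is one sentence in each of the two sections and one date per patient, with no extra patients, visits or staff. The downside is small: the model assumes a constant event rate over the observed window.

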### Patients

In total, 45 PD patients (age 40 or older) with Hoehn and Yahr stages II-IV (only mobile patients with advanced PD), with at least one fall or near-fall within the 3 months before baseline assessment, will be asked for participation when appointed to in-ward neurorehabilitation at the Center for Neurorehabilitation in Valens, Switzerland (Figure 1). Patients shall be able to participate in the treadmill training at high intensity for 3 weeks. Patients with dementia, defined by a Mini-Mental Status Examination (MMSE) test result of <24, will be excluded from participation. The protocol was approved by Ethikkommission Ostschweiz (BASEC ID 2019-01894) and registered at ClinicalTrials.gov (Identifier: NCT04108741).

### Experimental Intervention

All three arms of the study will get their usual in-ward rehabilitation with additional treadmill sessions 5 times weekly for 3 weeks. The three treadmill sessions vary only with respect to the AR and the RNG component added to TT alone. The three groups will be trained at 70% of the maximal convenient velocity of each patient to train with high intensity as suggested (33). A recent meta-analysis showed that high-intensive training (HIT) is feasible and safe in persons with PD (34). The authors concluded that there is clear and strong evidence for resistance training to improve muscle strength and moderate evidence for endurance training to improve cardiorespiratory fitness. The speed will be increased stepwise according to baseline measurements. For TT, we will employ the AR-based treadmill from Motek (C-Mill, Motek Medical B.V., The Netherlands, Figure 3).

**Figure 3 F3:**
[figure not shown]
Treadmill training by using the C-Mill (MOTEK, the Netherlands) which may include training on a display and on the floor (augmented reality).

In the AR group, different mixed programs (based on the standard software) adapted to the need of PD patients with balance deficits were designed for each week to increase difficulty (e.g., stepping stones, speeding-up) for 30 min for 5 days a week for 3 weeks. Stepping stones consist of virtual barriers displayed on the treadmill ground to train external cueing. In the subprogram “speeding-up,” patients can change their velocity according to signs on the floor to train their walking flexibility. At the end of the treadmill training, we selected a longer period from 5 to 6 min with a complex dual-task paradigm with increased difficulty in each week. In the first week, we will employ the “Italian Alps.” Italian Alps consists of an AR with a DT displayed on a display in front of the patients. While walking, the patient move to collect the ingredients for a pizza displayed on the way on different sides. These ingredients can be reached by moving sideward but only necessary ingredients shall be taken as displayed on the screen. In the second week, we will use “Arcanoid.” This is a balance game on the display in which the patients have to reduce the geometric figures at the top by moving a ball that hits a plate on the bottom that can be moved by their feet. In the third week, we will administer “Monster Games.” In Monster Games, the patients have to decide whether to pick up a reward or to avoid a monster on the floor of the treadmill. Most games give a visual feedback either on the display or on the treadmill floor. There is also an auditory feedback provided in some applications but turned off for the present investigation.

In the RNG-TT group, we employ TT as described above but with RNG as the simultaneous secondary task. RNG will be performed every second day during treadmill training (4 blocks of 100 s each, separated by 4-min blocks of pure walking). Specifically, the Mental Dice Task (35, 36) will be administered. During 100 s, patients have to produce the digits of a single die in a sequence as random as possible. The generation will be individually paced, i.e., in a rhythm provided by the patient's gait, such that one number for every right-foot placement will be to be generated. Number generation will be tape-recorded, and the sequence will be later analyzed to characterize its information-theoretic properties (omitted steps and “rule breaks,” i.e., digits like 7, will also be recorded). This will allow quantification of the interference between walking and number generation. Every second session will be administered under dual-task conditions.

In the TT group, we will also employ the C-Mill treadmill, but use the display only for walking purposes without any tasks. Walking speed will be increased stepwise in analogy to the other interventions.

